### Harms

Adverse events if any, which are directly related to the study intervention, will be monitored and assessed by researchers involved in the study. The patient will be on continuous monitoring. Any such adverse events that arise during the study will be reported to Kashan University of Medical Sciences and the Ethics Committee of Kashan University of Medical Sciences. Any such events will be managed by the treating physician and the cost for the same will be covered under the trial fund.

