**Methods:**

This is an open-label randomized controlled trial to evaluate the effect of daily calorie restriction (control) and modified intermittent fasting (intervention) on sleep quality, anthropometric data, and body composition in women with obesity or overweight for 8 weeks. Fifty-six participants will be classified using stratified randomization based on body mass index (BMI) and age. Then, participants will be assigned to one of the two groups of intervention or control using the random numbers table. The sleep quality, daytime sleepiness, and insomnia will be evaluated by using the Pittsburgh Sleep Quality Index (PSQI), the Epworth Sleepiness Scale (ESS), and the Insomnia Severity Index respectively. The primary outcomes chosen for the study were as follows: the difference in sleep quality, daytime sleepiness, insomnia, BMI, fat-free mass (FFM), body fat mass, waist circumference, and waist-to-hip ratio from baseline to 8 weeks. Secondary outcomes chosen for the study were as follows: the difference in hip circumference, the visceral fat area, percent body fat, soft lean mass, skeletal muscle mass, extracellular water ratio, and total body water from baseline to 8 weeks.

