### Randomization

Fifty-six participants will be selected from the Health Centers of Kashan University of Medical Sciences by Simple Random Sampling according to the inclusion and exclusion criteria. A trained nutritionist will enroll participants. Eligible participants will be stratified by age and BMI to ensure between-group homogeneity. Participants per stratum will be assigned to one of the two groups “modified intermittent fasting” (intervention) and “daily calorie restriction” (control) after baseline investigations. Individuals cannot be blinded to allocation because of the nature of the intervention. An independent statistician will generate the allocation sequence by using random numbers’ table and the statistician will be blinded throughout the entire trial.

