### Plans for participant retention and adherence to the diet

To control the adherence to the diet by the participants, once every 2 weeks, food record questionnaires will be completed 3 days (two normal days and one day off) a week. Researchers will make regular phone calls to participants to reinforce what they will be doing and to encourage them to continue. Also, participants will be monitored in weekly phone interviews. The data of subjects who discontinue or deviate from intervention protocols for any reason will be analyzed with intention-to-treat.

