### Roles and responsibilities

This study will be conducted in Shahid Beheshti Hospital, Kashan. The trial will be run on an individual basis by the principal investigators. The study will be overseen by the scientific committee every week or when the need arises, in case of any adverse events. Kashan University of Medical Sciences will oversee the overall conduct of the trial. The study team will meet and discuss the problems in the operation of the study every week. DMC will be not needed for the study as the study will involve a small group of patients and will be in a single center.

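### Adverse event monitoring and reporting are limited to events judged related to the intervention, by study researchers in an open-label trial; no all-cause collection rule is stated

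*Protocol article*

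**What the plan says.** The Harms section fixes which events are followed and by whom: "Adverse events if any, which are directly related to the study intervention, will be monitored and assessed by researchers involved in the study". It then states "The patient will be on continuous monitoring", without a method or frequency. The next sentence returns to the restricted set of events: "Any such adverse events that arise during the study will be reported to Kashan University of Medical Sciences" (and to the Ethics Committee).

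On blinding, the abstract calls the trial open-label and attaches the arm labels: "This is an open-label randomized controlled trial to evaluate the effect of daily calorie restriction (control) and modified intermittent fasting (intervention" being the label of the fasting diet. The Randomization section adds "Individuals cannot be blinded to allocation because of the nature of the intervention". The only role described there as blinded is the statistician: "the statistician will be blinded throughout the entire trial".

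On contact and oversight, the section on retention and adherence says that "participants will be monitored in weekly phone interviews", and Roles and responsibilities says "DMC will be not needed for the study". That section also describes oversight by a scientific committee, and the auditing section describes weekly site checks by a team said to be independent of the authors. The Statistical assessment section plans to report reasons for withdrawal by randomised group and to compare them qualitatively.

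**The concern.** An article may leave forms, grading scales and coding to the full protocol. This one goes further and states an inclusion rule: the events to be monitored and reported are those related to the intervention. Causality then has to be judged before an event enters the safety record, by people who are not described as blinded to the diet.

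Two things are at stake:

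- **Counts by arm.** If related events are tabulated by arm, the table mixes how often events happened with how often staff blamed the diet. The two cannot be separated afterwards if the remaining events were not collected.
- **Unexpected harms.** An effect that nobody anticipates is the least likely to be called related when it occurs, so a relatedness filter is weakest where safety data are most needed.

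The wording has a further ambiguity. The term intervention is also the name of the fasting arm, so a literal reader could apply the rule to fasting-related events only and leave daily calorie restriction without any stated collection of harms.

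**Working it through.** The plan gives no harms figure to reproduce. The check is first a reading of every section that could widen the rule, then a short formula for what the rule does to counts.

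**1. Does any other section set a wider rule?**

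| Section | What it provides | Does it set all-cause collection? |
|---|---|---|
| Harms, continuous monitoring | A general statement, no method | No; the next sentence returns to the restricted events |
| Roles and responsibilities | Committee oversight weekly or as needed, with adverse events as a trigger | No; it says who oversees, not what is recorded |
| Retention and adherence | Weekly phone interviews | No; no adverse event questions are mentioned, though the contact is suitable for them |
| Statistical assessment | Reasons for withdrawal by group | No; it covers only women who leave |
| Auditing | Weekly checks of data quality, database, materials and consent | No; it checks what has been recorded |

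**2. Which arm does the rule cover?** The abstract and the Randomization section use intervention for fasting and control for daily calorie restriction. The section on discontinuation criteria speaks of allocated interventions for any participant, which supports a reading that covers both diets. The text does not settle the matter.

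**3. Effect on recorded counts, taking the rule to cover both arms.** Let p be the true event risk in an arm and a the probability that an event there is judged related. The recorded risk is p × a, so

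recorded ratio = (p_F / p_C) × (a_F / a_C),

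where F is fasting and C is control.

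The arm size of 28 comes from the sample size section. All values of p and a below are assumptions.

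| p_F, p_C | a_F, a_C | Recorded risks | Expected women recorded (of 28) | True ratio | Recorded ratio |
|---|---|---|---|---|---|
| 20%, 20% | 80%, 80% | 16%, 16% | 4.5, 4.5 | 1.0 | 1.0 |
| 20%, 20% | 80%, 40% | 16%, 8% | 4.5, 2.2 | 1.0 | 2.0 |
| 20%, 20% | 90%, 30% | 18%, 6% | 5.0, 1.7 | 1.0 | 3.0 |
| 40%, 20% | 40%, 80% | 16%, 16% | 4.5, 4.5 | 2.0 | 1.0 |

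For example, in the second row 28 × 0.20 × 0.80 = 4.48 and 28 × 0.20 × 0.40 = 2.24. The last row shows a true excess hidden by attribution in the other direction: 0.40 × 0.40 = 0.20 × 0.80 = 0.16. With equal true risks the recorded ratio is a_F / a_C whatever the size of the risk. If a_F = a_C, the ratio is undistorted.

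**The case against.** The strongest reply is that this criticises a comparison the protocol does not make. No adverse event outcome appears among the 8 primary or 7 secondary outcomes, and the Statistical assessment section plans no test or estimate of harms by arm. That is correct, and it limits the point to safety recording and reporting. It does not remove the point, because the stated purpose is to inform dietary recommendations, and readers will look at any harms reported by arm.

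Second, the text never says that unrelated events are discarded. A reader might infer that they leave no record at all, but the documents do not support that: they say what is monitored and reported, and are silent on the rest. Nor do they say outright who decides relatedness; that it is the study researchers is implied by their role as assessors.

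Third, oversight is wider than the absence of a DMC suggests. There are a scientific committee and an audit team, and withdrawal reasons by group give some tolerability information that does not pass through attribution. This stands, but none of it tells staff to record events regardless of cause.

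Fourth, a reader might infer that symptoms would naturally be blamed on fasting because control women eat every day. The Intervention section does not support that contrast. Fasting women also eat on fast days, and the average intake prescribed is (25% + 100%) / 2 = 62.5% of requirement, against 63% daily in control. Neither the presence nor the direction of differential attribution can be taken from the documents.

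Finally, checklists and tables are operational detail that an article may omit. Their absence is not the point; the restrictive rule that is stated is.

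**Conclusion.** The concern holds in a limited form. The protocol article states a relatedness filter for adverse event monitoring and reporting, applied by study researchers in an open-label trial, and no section replaces it with all-cause collection. Followed as written, it would make harm counts by arm depend on unblinded attribution and could let unexpected harms go unreported.

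The size cannot be estimated from the documents. The recorded ratio differs from the true one by the factor a_F / a_C, which was 1 to 3 in the assumed scenarios with equal true risks and 0.5 in the one where a true excess is hidden. These figures restate the assumptions and show the mechanism; they do not forecast a bias. A reader might conclude that the arms' harms cannot be compared without bias. That goes too far: bias arises only if attribution differs between arms. The document neither shows that it will nor contains anything to prevent it.

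The efficacy analyses are not touched. This is a cheap improvement to safety data, worth making because events not recorded at the time are hard to recover later.

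**What to change.** Reword the Harms section so that:

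1. All adverse events, whatever the presumed cause, are recorded in both arms, naming both diets so that the term intervention cannot be read as fasting only.
2. The same questions are put to all women at the weekly phone interviews already planned.
3. Relatedness is entered afterwards as a separate field, preferably by someone unaware of the allocation.
4. The number of women with any adverse event and with any serious adverse event is reported by randomised arm, descriptively and without a formal test.

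The cost is a few questions on existing calls, slightly more data entry and one more table. No change to sample size, outcomes or efficacy analysis is needed.

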### Frequency and plans for auditing trial conduct

The study team will meet every week and will conduct at least one on-site visit every week to check the quality of the data, database operation, subject material, and informed consent. This team, totally independent from the authors and competing interests, will have the full right to make the final decision on the trial status.

## Discussion

Given that one of the major causes of sleep disorders is obesity, weight-loss approaches can affect sleep quality. In recent decades, the fasting diet has emerged as a popular option for weight loss. Human trials that investigate the effect of intermittent fasting on sleep quality and sleep disturbances are limited. Also, studies that have investigated the effect of intermittent fasting and daily calorie restriction on anthropometric indices have not reached definitive results. Hence, our study aims to investigate the effect of 8 weeks of intermittent fasting intervention compared with daily calorie restriction on sleep quality and anthropometric indices. The information gained will enhance our understanding of fasting interventions, which can be used to improve clinical dietary recommendations.

### Protocol amendments

Any change in the conductance of the study made in the protocol will be informed in the specified format to Kashan University of Medical Sciences and the IRCT. As the study has followed up, the patients who will be present in the study will be informed about the protocol changes.

## Trial status

Recruitment for the trial starts in September 2022 and is expected to continue recruitment until late December. This is protocol version 1, July 29, 2022.

## Data Availability

The datasets used and analyzed during the study will be available from the corresponding author upon request.

## Appendix

Consent materials: A sample consent form is provided as an appendix to this manuscript. Biological specimens: Laboratory evaluation and storage of biological specimens are not applicable in the current trial.

## Abbreviations

BMI: Body mass index
PSQI: Pittsburgh Sleep Quality Index
FFM: Fat-free mass
MET: Metabolic equivalents
